#### Process evaluation

This will comprise case studies at 2–4 intervention sites. At each site, we will conduct semi-structured, face-to-face, video call or telephone interviews with 8–10 participants, 3–5 relatives/ friends (study partners who have attended groups or otherwise supported participants) at 6 months, with a further brief interview at 12 months to investigate impacts during the less intensive stage of the intervention, between 6 and 12 months. All facilitators will be interviewed at 12 months, or sooner if they leave the project. Qualitative interviews will take place after quantitative outcomes have been collected at each time point to build on any reflections prompted by quantitative measures being administered. We will also conduct semi-structured, face-to-face or telephone interviews with 5–6 participants who leave the intervention prematurely.

The sampling strategy and topic guides are designed to test a priori theories about how the intervention works, and causal assumptions regarding intervention mechanisms that were developed during co-design and iterated by the team and PPI group (see Supplementary file for logic model). Interviews explore how participants experienced the intervention, how it might have supported them to make and maintain lifestyle changes, and their perceived impact of these, including on memory. We are, in addition to the main process evaluation, conducting 10–15 photo-elicitation interviews to explore the meanings participants attribute to photographs they donated to the study archive. Interviewees for these additional interviews are be purposively selected for ethnic diversity, as part of a sub-study exploring how dementia prevention messages are understood and experienced across different ethnic and cultural contexts.

We are also exploring how the intervention is implemented within the study (content/fidelity, frequency/duration, and coverage/reach). We are audio-recording one randomly selected group intervention session from each cohort to assess facilitator fidelity to the manual using a standard checklist which we have developed. We record attendance at intervention components, goals set and whether they are achieved using a standardised spreadsheet completed during goal phone calls, and information on use of cognitive training will be downloaded from the study website.

### Participant timeline {13}

Table 1 provides an overview of the timeline for enrolment, outcome assessments and intervention delivery. S_1-10_ refers to the 10 group intervention sessions, 6M, 12M and 24M refer to the follow-up assessments at 6, 12 and 24 months from baseline.

**Table 1 Tab1:** Participant timeline

	Enrolment	Baseline													
**TIMEPOINT**	−*t*_1_	0	s_1_	s_2_	s_3_	s_4_	s_5_	s_6_	s_7_	s_8_	s_9_	s _10_	6M	12M	24M
**ENROLMENT:**															
Eligibility screening	X														
Informed consent		X													
Randomisation		X													
**INTERVENTION:**															
Sessions 1–10			X	X	X	X	X	X	X	X	X	X			
**ASSESSMENTS:**															
Demographics		X													
NTB		X												x	X
CSRI		X												X	X
EQ-5D-5L		X												X	X
FAQ		X												X	X
PSQI		X												X	X
HADS		X												x	X
MDS		X											X	X	X
24-h food recall		X												X	X
AUDIT		X												X	X
Smoking status		X												X	X
PSNS, LTE, BLS		X												X	X
GHQ-12		X												X	X
PM		X												X	X
PA		X												X	X
Bloods and saliva		X												X	X
Qualitative interviews (intervention arm)													X	X	

Legend: *AUDIT* Alcohol Use Disorders Identification Tool, *BLS* brief loneliness scale, *CSRI* Client Service Receipt Inventory, *EQ-5D-5L* EuroQoL EQ-5D 5 Level, *FAQ* Functional Assessment Questionnaire, *GHQ-12* General Health Questionnaire-12, *HADS* Hospital Anxie**t**y and Depression Scale, *LTE* list of threatening experiences, *MDS* Mediterranean Diet Score, *NTB* Neuropsychological Test Battery, *PSQI* Pittsburgh Sleep Quality Index, *PA* physical activity (step count) and resting heart rate (over 2 weeks), *PM* physiological measures (gait speed, grip strength, weight, body mass index, and hip and waist circumference), PSNS primary support network size

### Sample size {14}

The trial aims to recruit 704 participants (352 per randomised group). We calculated that this number is sufficient to detect, with 90% power and 5% significance, a difference of 0.15 in average NTB scores between intervention and control groups at 2 years (assumed standard deviation = 0.6) [34]. The calculation is based on an analysis that adjusts for baseline NTB score (assumed correlation coefficient between baseline and 24-month scores of 0.6) [34], intervention arm clustering (assuming an average of 36 participants per facilitator [32] after drop-out), an intracluster correlation coefficient of 0.03 and 10% drop-out. The initial calculation used unequal allocation (ratio 1:0.52), so that after inflation for clustering in the intervention arm, the allocation ratio is 1:1.

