*Secondary outcome* measures are:Modified version of the Client Service Receipt Inventory (CSRI) for self-reported health and social care resource use [21]EuroQoL EQ-5D 5 Level (EQ-5D-5L) to measure preference-based health-related quality of life [22]Hospital Anxiety and Depression Scale (HADS) [23]Mediterranean Diet Adherence Score (MEDAS) assesses adherence the plant-based Mediterranean style diet intervention elements [24]MyFood24, a validated 24-h recall tool for dietary assessment [25], which in addition to capturing adherence to the APPLE Tree dietary goals, provides details of participants habitual diet. Participants provide details of all food and drink consumed the day before the assessment, and this is logged by researchers on the MyFood24 online tool.Pittsburgh Sleep Quality Index [26]Alcohol Use Disorders Identification Tool (AUDIT-C) to measure alcohol consumption [27]Primary support-network size [28]Brief loneliness scale [29]Smoking status (smoker versus non-smoker);Physiological measures including gait speed, grip strength [30], weight and body mass index (BMI),Physical activity and average heart rate (resting and high) over 2 weeks, using data downloaded from wearable sensors (Garmin) [31];Blood indices of dietary compliance (red blood cell omega-3 index and vitamin C); and cardiovascular and cognitive biomarkers of risk (plasma total, LDL and HDL cholesterol, triglycerides, glucose, HBA1c (as a measure of glucose tolerance), BDNF and insulin).

Informants will be asked to complete the following secondary measures:Functional Assessment Questionnaire measuring participants’ activities of daily living [16]General Health Questionnaire (GHQ-12) with regard to their psychological health [32].

All primary and secondary outcome measures are obtained at baseline, 12-month and 24-month follow-up. In addition, the MEDAS is collected at 6 months, to explore dietary changes in detail during and after the intervention.

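### The printed cluster size does not give the stated 704 and 1:0.52 (about 32 per facilitator after drop-out does), and the 90% power makes no allowance for few facilitator clusters

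*Protocol article*

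**What the plan says.** All the inputs are in the protocol article, Sample size {14}:

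- Size: "The trial aims to recruit 704 participants (352 per randomised group").
- Target: "with 90% power and 5% significance, a difference of 0.15 in average NTB scores", with "assumed standard deviation = 0.6".
- Baseline adjustment: "assumed correlation coefficient between baseline and 24-month scores of 0.6".
- Clustering and loss: "assuming an average of 36 participants per facilitator [32] after drop-out", and "an intracluster correlation coefficient of 0.03 and 10% drop-out".
- Allocation: "The initial calculation used unequal allocation (ratio 1:0.52), so that after inflation for clustering in the intervention arm, the allocation ratio is 1:1".

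Three other places bear on the point. Outcomes {12} cites the same reference number for an informant questionnaire: "General Health Questionnaire (GHQ-12) with regard to their psychological health [32"]. Intervention description {11a} has two facilitators deliver each group, and no total number of facilitators is given. The primary outcome analysis is a mixed-effects regression that allows for facilitator clustering in the intervention arm only. It names no degrees-of-freedom method, and the detail is deferred to a separate analysis plan.

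**The concern.** Cluster size fixes the design effect, and the design effect fixes both the pre-inflation ratio and the total. If the printed caseload is taken at face value, the ratio and the total do not follow from it. Anyone who re-checks power, or updates it with the observed facilitator load, would start from 2.05 when the calculation evidently used about 1.93.

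The second issue is the reference distribution. A design effect allows for the extra variance that clustering causes. It does not allow for having to estimate that variance from a small number of facilitators. The sample-size section claims 90% power and 5% significance together. With few clusters on one side, the stated size may not deliver both.

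**Working it through.** **Inputs (Sample size {14}).** Difference 0.15; SD 0.6; correlation 0.6; intracluster correlation 0.03; drop-out 10%; 352 per arm. Two-sided 5% is assumed, since the article does not state the sides and two-sided fits its figures.

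**Base quantity.** SD after baseline adjustment = 0.6 × √(1 − 0.36) = 0.48. Then (1.960 + 1.2816)² × 0.48² / 0.15² = 107.6. With a design effect DE on the intervention arm only and equal final arms, analysed n per arm = 107.6 × (1 + DE). The pre-inflation ratio that ends at 1:1 is 1/DE, where DE = 1 + (m − 1) × 0.03. Dividing by 0.9 allows for drop-out.

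**Which cluster size m reproduces the stated figures?**

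| m after drop-out | DE | 1/DE | Analysed per arm | Recruited per arm | Total |
|---|---|---|---|---|---|
| 32 | 1.93 | 0.518 | 315.3 | 350.3 | about 701 |
| 32.4 (= 36 × 0.9) | 1.942 | 0.515 | 316.5 | 351.7 | about 703, or 704 with whole participants per arm |
| 36 (as printed) | 2.05 | 0.488 | 328.2 | 364.6 | about 730 |

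The stated ratio of 0.52 and total of 704 match the first two rows, allowing for rounding. They do not match the third: 0.52 × 2.05 = 1.07, so a start at 0.52 would not end at 1:1.

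**Power at 704, large-sample.** Analysed n per arm = 352 × 0.9 = 316.8.

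- m = 32: SE = 0.48 × √((1 + 1.93)/316.8) = 0.0462; 0.15/0.0462 = 3.249; power = Φ(3.249 − 1.960) = 90.1%. This reproduces the stated 90%.
- m = 36: SE = 0.0471; 0.15/0.0471 = 3.185; power = 89.0%.

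**How many clusters?** The article does not say. Its caseload implies 352/36 = 9.8, or 316.8/32 = 9.9, so about ten if each participant belongs to one facilitator or one fixed pair. If both facilitators of a group are counted separately, 2 × 352/36 = 19.6, so about twenty.

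**Power at 704 with a test that holds 5%.** Let V_C = 0.48²/316.8 = 0.000727 and V_I = 1.93 × V_C = 0.001404. Satterthwaite df = (V_I + V_C)² / (V_I²/(K − 1) + V_C²/(n − 1)), and power comes from the noncentral t with noncentrality 3.249.

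- K = 9.9: df = 20.4, critical value 2.084, power 87.1%.
- K = 20 with the same design effect: df = 43.1, critical value 2.017, power 88.8%.

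A simulation of 200,000 trials with ten clusters of 32 gave 87.1% to 87.3% for the corrected test. The uncorrected normal test kept 89.7% power, at a type I error of 6.0%. The t approximation puts that error at 6.4% for about ten clusters.

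**The case against.** The strongest reply is that the sample size is not wrong. The stated ratio lets a careful reader recover the design effect that was used, 704 reproduces with about 32 per facilitator, and normal-approximation power is then 90.1%. That stands. A reader might infer from the printed sentence that the trial is short by about 26 participants (730 − 704). The document does not support this, because the ratio, the drop-out rate and the total agree with one another and only the printed caseload disagrees.

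On power, a reader might infer that the design delivers about 85%. That figure needs 36 per facilitator after drop-out and about nine clusters (85.1%), which is the reading the ratio and total rule out. Nor is ten a documented count: two facilitators share each group, and how they overlap across groups is not described. The power must therefore be stated conditionally.

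A reader might also add lower power and an inflated type I error together. They are alternatives: a corrected test gives about 87% power at 5%, while an uncorrected one keeps about 90% power at about 6%.

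The article does not say that a normal-based test will be used, and the degrees-of-freedom method may be in the analysis plan, which is not shown. Its absence from the article is not a fault.

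Finally, the shift is no larger than the uncertainty in the intracluster correlation. On the normal formula with 32 per facilitator, 0.02 gives 93% and 0.04 gives 87%. That is true and limits the weight of the point. It does not remove it, because the loss from few clusters arises at the article's own value of 0.03.

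**Conclusion.** The sample-size section contradicts itself. The printed caseload implies a ratio of 0.49 and about 730 participants, against 0.52 and 704. The contradiction is resolved by 36 before drop-out and about 32 after. That the bracketed 32 is this number turned into a citation is an inference, though a strong one: it stands where the number belongs, and the same reference supports the GHQ-12, an unlikely source for a facilitator caseload.

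The stated 90% is a large-sample figure. With a test that holds 5%, the power of 704 is about 87% with ten clusters of 32 and about 89% with twenty, a shortfall of roughly 1 to 3 points. This assumes equal caseloads, independent clusters and the article's own inputs. Unequal caseloads would lower power further. The point is worth correcting. It does not call the target into question.

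**What to change.** 1. Check the original calculation. If it confirms the reading above, reword the caseload in Sample size {14} as an average of 36 participants per facilitator at recruitment, with 32 remaining after drop-out, and remove the citation mark.
2. State the expected number of facilitators and whether they work as fixed pairs or overlap across groups. Restate the power of 704 as about 87–89%, conditional on that number.
3. Confirm that the primary mixed model uses a small-sample degrees-of-freedom method for the treatment effect (Satterthwaite or Kenward-Roger). If the analysis plan already says so, nothing more is needed.

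The target of 704 stays. The cost is a change of wording and a slightly less favourable stated power.

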### Recruitment {15}

Recruitment sources are described in the study setting section {9}. Those interested in participating receive a Participant Information Sheet (PIS). A researcher then arranges an appointment to meet with them (video call or face-to-face) for a screening interview and, if they are eligible, elicit informed consent and conduct the baseline assessment.

We estimate that we will achieve recruitment of 704 participants within a 27-month period between October 2020 and December 2022. This equates to recruitment of 26 participants per month. In order to reach our recruitment target, participants are recruited through a range of recruitment sources, including primary care practices, memory services, NGOs for older people, the Join Dementia Research register, social media and the study website. We also advertise in local newspapers, and we are recruiting participants in response to an article about the study in a national newspaper.

## Assignment of interventions: allocation

### Sequence generation {16a}

Randomisation is at the level of the individual participant using a web-based application; Sealed Envelope, provided by Priment Clinical Trials Unit (CTU). Randomisation is blocked and stratified by site.

### Concealment mechanism {16b}

Details of treatment arm allocation are stored in a section of the Sealed Envelope database, to which blinded assessors do not have access. The trial manager and researchers involved in intervention procedures are informed of the randomisation outcome.

### Randomisation process {16c}

Researchers enrol participants in the Sealed Envelope database once the screening and baseline data has been collected. A member of the research team who is not blinded to treatment allocation then undertakes the randomisation. Participants are assigned to treatment groups through consecutive allocation of participant numbers and use of a Trial Participant Log.

## Assignment of interventions: blinding

### Who will be blinded {17a}

This is a single-blind study. Researchers conducting follow-up outcome measures are blind to participants’ treatment arm allocation. Study participants and their informants and researchers facilitating the intervention are aware of the participant’s treatment arm allocation due to the nature of the intervention. Statisticians are not be blinded, as due to clustering in the intervention arm, group allocations will be apparent when managing data.

### Procedure for unblinding if needed {17b}

There are no plans for intentional unblinding. In the unlikely event of a probable intervention-related SAE (serious adverse event), we will follow PRIMENT CTU procedures for unblinding. If a researcher becomes unblinded, the study team record this and ask an alternative blinded researcher to complete future outcome measures for that participant.

## Data collection and management

### Plans for assessment and collection of outcomes {18a}

Researchers assess outcome measures at baseline, 12 months and 24 months post-randomisation. In addition, the MEDAS is conducted for all participants at 6 months, as part of a sub-study to explore dietary changes in greater depth. A full list of primary and secondary outcome measures is provided under ‘Outcomes {12}’, and timelines are outlined in Table 1. Outcome measures and interviews are conducted by researchers fully trained in the study measures and conducting qualitative interviews.

### Plans to promote participant retention and complete follow-up {18b}

Each participant is offered a £20 gift voucher after completion of each outcome assessment (baseline, 12- and 24-month follow-ups) to thank them for their time. A further £20 gift voucher is offered to each participant taking part in a process evaluation qualitative interview. If required, the outcome measures are conducted over two separate visits. Participants who indicate that they do not have time to complete follow-up have the option to complete the primary outcome only.

### Data management {19}

Data is collected from participants manually on trial-specific paper Case Report Forms (CRFs) that are stored securely at UCL and entered into the database, managed by Sealed Envelope. Sealed Envelope has been assessed by the Priment CTU to ensure that adequate processes are in place and are being followed for quality management, software and security. Intervention sessions and qualitative interviews are recorded using a password-protected, encrypted recorder, and files are transferred between professional transcription services and UCL via a secure server hosted by the transcription service. All identifiable information is removed from the transcripts including any reference to names or places. Audio files are password-protected and stored in separate folders to the transcripts on secure servers and only accessible to those authorised to use the files.

### Confidentiality {27}

The CRFs do not bear the participant’s name. Personal data needed to re-contact participants is held on secure servers. Consent forms are held manually in locked filing cabinets on University premises, and only named research team members have access.

### Plans for collection, laboratory evaluation and storage of biological specimens for genetic or molecular analysis in this trial/future use {33}

Samples are collected by participants at home, and we provide instructions and appropriate equipment. Dried bloodspot sample cards are posted to UCL and stored at −80 °C and saliva samples at room temperature.

## Statistical methods

### Statistical methods for primary and secondary outcomes {20a}

Statistical analyses will be described in a predefined detailed statistical analysis plan agreed prior to commencement of data analysis and conducted according to ICH E9 and PRIMENT CTU standard operating procedures [35].

## Summary of baseline data and flow of trial participants

Participants’ baseline characteristics will be described by treatment group using summary statistics (means (standard deviations), medians (with interquartile ranges), counts and proportions, as appropriate). A CONSORT diagram will describe the flow of participants through the trial including numbers eligible, randomised, and consenting and with data available for the primary outcome (http://www.consort-statement.org/). The number of participants withdrawing from the intervention and the study and reasons where supplied will be reported.

## Primary outcome analysis

For each randomised group, we will summarise the primary outcome (NTB scores at 24 months) using means with standard deviations and graphically examine the distribution of the score. The effect of the intervention will be described using the between-group difference in means calculated with a 95% confidence interval. This estimate will be obtained from a mixed-effects multiple regression model adjusting for baseline NTB score and site and allowing for facilitator clustering in the intervention arm [36]. The intracluster correlation (with 95% confidence interval) will be calculated to describe the extent of facilitator clustering. All analyses will be carried out on an intention-to-treat basis comparing the groups as randomised using all available data.

NTB scores at 12 months will also be summarised by treatment group using descriptive statistics. Profile plots will be used to illustrate trends in the average scores over time (baseline, 12 months and 24 months). The mixed-effects model will be extended to include the 12-month measurement and to consider the effect of the intervention over time by including a treatment-group-by-time interaction.

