### Outcomes {12}

The *primary outcome* is cognition, measured using the Neuropsychological Test Battery (NTB) composite score (video call or face-to-face assessment) at 24 months. It is highly sensitive to change with excellent internal consistency and test-retest reliability [19]. It is validated for delivery by video call [20]. It comprises tests of memory, executive function, and paired associates learning and has nine validated components:Wechsler Memory Scale visual paired associates immediate recall (WMS-R) (score range, 0–18)Wechsler Memory Scale visual paired associates delayed recall (WMS-R) (range, 0–6)Wechsler Memory Scale logical memory immediate recall (WMS-IV) (score range 0–25)Wechsler Memory Scale logical memory delayed recall (WMS-IV) (score range 0–25)Wechsler Memory Digit Span—forwards (WAIS-IV) (score range, 0–16)Wechsler Memory Digit Span—backwards (WAIS-IV) (score range, 0–16)Rey Auditory Verbal Learning Test (RAVLT) immediate (RAVLT-I) (score range, 0–105)RAVLT delayed (RAVLT-D) (score range, 0–15)Controlled Word Association Test (COWAT)Category fluency test (CFT)

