To align the economic evaluation with the primary outcome, the primary analysis for the economic evaluation will be complete case with sensitivity analyses adjusting for predictors of missingness and multiple imputation (see section ‘Methods in analysis to handle protocol non-adherence and any statistical methods to handle missing data {20c}’). Two-part bootstrapping adjusting for baseline, site and including clustering will be used to construct cost-effectiveness acceptability curves of the probability that the intervention is cost-effective compared to the control for a range of cost-effectiveness thresholds for a QALY gained and unit change in NTB. Additional sensitivity analyses will be performed, where relevant, to assess the impact of alternative modelling assumptions on the results, including projecting 6-month resource use collected at 12 and 24 months over the full 12-month time-period between follow-ups.

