### Methods in analysis to handle protocol non-adherence and any statistical methods to handle missing data {20c}

Where there is missing outcome data, the main analyses will be based on available data, relying on an assumption that data is missing at random. Reasons for missingness will be described, and frequency (%) of subjects with missing data, by reason, will be provided for each randomised group (and for each outcome). Characteristics of participants with and without missing outcome data will be compared using logistic regression models (with missing yes/no as the outcome) to identify characteristics associated with missingness. In a sensitivity analysis, the treatment effect will be re-estimated with additional adjustment for baseline predictors of missingness. Further sensitivity analyses based on multiple imputation methods will be considered if appropriate.

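### The primary estimate comes from a 24-month-only model, so drop-out that follows decline already recorded at 12 months is left to an analysis with no stated missing-data role

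*Protocol article*

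**What the plan says.** All references are to the protocol article.

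- **Outcomes {12}:** the primary outcome is cognition, "measured using the Neuropsychological Test Battery (NTB) composite score (video call or face-to-face assessment) at 24 months". All primary and secondary measures are also taken at 12 months.
- **Primary outcome analysis:** the between-group difference comes from a mixed-effects regression of 24-month NTB, adjusted for baseline NTB and site, with facilitator clustering in the intervention arm. A second step follows: "The mixed-effects model will be extended to include the 12-month measurement and to consider the effect of the intervention over time", through an arm-by-time interaction. This second model is not called primary and is given no missing-data purpose.
- **Section {20c}:** "the main analyses will be based on available data, relying on an assumption that data is missing at random". Reasons for and frequency of missingness are reported by arm, and its predictors are explored by logistic regression. One sensitivity analysis is committed: re-estimation with extra adjustment for baseline predictors of missingness. Beyond that, "Further sensitivity analyses based on multiple imputation methods will be considered if appropriate".
- **Economic evaluation:** "To align the economic evaluation with the primary outcome, the primary analysis for the economic evaluation will be complete case". This supports reading the primary clinical analysis as one of participants with a 24-month score.

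**The concern.** In a model whose only outcome is 24-month NTB, a participant seen at 12 months but lost by 24 months contributes nothing to the estimate. The missing-at-random assumption is then conditional on arm, baseline NTB and site. It fails if, among people alike on those, the ones who declined in the first year are more likely to leave.

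That is plausible here. Participants are recruited for high dementia risk, and a participant who loses capacity continues only if a consultee agrees ({26a}). The dependence could also differ by arm. Participants know their allocation. One arm has group sessions, tea breaks and goal calls, with monthly contact up to month 12, while the other has usual care and a brochure.

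Adding baseline covariates cannot repair this, because the information that predicts drop-out arises after baseline. What is at stake is a shift of the primary effect in either direction, although the score needed to correct much of it will have been collected.

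**Working it through.** **1. The plan's own figure.** Inputs from Sample size {14}: "with 90% power and 5% significance"; difference 0.15 and SD 0.6; "assumed correlation coefficient between baseline and 24-month scores of 0.6"; ICC 0.03; 36 participants per facilitator; 10% drop-out. A two-sided test is assumed.

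- Residual SD = 0.6 × √(1 − 0.6²) = 0.48.
- With cluster size 36 × 0.9 = 32.4, the design effect in the intervention arm is 1 + 31.4 × 0.03 = 1.942. Its inverse is 0.515, close to the stated 0.52.
- n per arm = (1 + 1.942) × [0.48 × (1.960 + 1.282) / 0.15]² = 316.5. Divided by 0.9 this is 351.7, so 352 per arm and 704 in total, as stated.
- SE = 0.48 × √(2.942 / (352 × 0.9)) = 0.046. With cluster size 36 it is 0.047, which changes nothing below.

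**2. Drop-out that depends on change from 0 to 12 months.** This was checked by large-sample simulation (500,000 per arm). The following are assumptions, not figures from the article: correlation 0.6 between baseline and 12 months and 0.7 between 12 and 24 months; logistic drop-out with log-odds 1 per SD of 0–12 month change; everyone has a 12-month score. The true effect is 0.15.

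| Dependence on change | Missing | 24-month-only estimate |
|---|---|---|
| Intervention arm only | 10% | 0.173 |
| Control arm only | 10% | 0.129 |
| Intervention arm only | 20% | 0.190 |
| Control arm only | 20% | 0.108 |
| Equal in both arms | 10–20% | 0.147 to 0.151 |

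Using the 12-month score for those lost by 24 months gives 0.149 to 0.152 in the one-arm scenarios.

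**3. Drop-out that depends on the 12-month level instead of change.** The 12-to-24-month correlation was varied from 0.6 to 0.8, with log-odds 0.7 or 1 per SD and about 10–12% missing. The 24-month-only estimate is 0.129 to 0.177 if the dependence is in one arm only, and 0.147 to 0.149 if it is equal. Using the 12-month score gives 0.148 to 0.151.

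**4. Size on the trial's scale.**

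- At 10% missing, 0.02 / 0.15 = 13% of the target effect, and 0.02 / 0.046 = 0.43 SE.
- At 20% missing, 0.04 / 0.15 = 27% of the target effect.
- With a true effect of 0.15 and a bias of −0.02, power is Φ(0.13 / 0.0463 − 1.96) = Φ(0.85), about 80% instead of 90%.
- With no true effect and a bias of +0.02, the two-sided false-positive rate is about 7% instead of 5%.

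**5. Drop-out that depends on unobserved 24-month scores.** The 12-month score does not settle this separate question. An observed 0.15 loses significance once bias exceeds 0.15 − 1.96 × 0.0463 = 0.059. If only intervention-arm drop-outs fall short, the shortfall needed is 0.059 / 0.10 = 0.59 at 10% missing, about one SD. At 20% missing it is 0.059 / 0.20 = 0.30, with the SE held at 0.046.

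**The case against.** The best defence is that a baseline-adjusted analysis at one time point matches the stated endpoint and the sample-size calculation, and that the 12-month model is planned beside it. The design also works against informative loss: a consultee route if capacity is lost ({26a}); vouchers, split visits and a primary-outcome-only option ({18b}); remote or face-to-face assessment ({9}). Missingness is to be reported by reason and arm. The bias needs a dependence that differs by arm, and at 10% drop-out it stays under half a standard error. Most of this stands. It limits the size of the problem, but it does not explain why the model that uses less of the collected data should carry the primary estimate.

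A reader might infer three stronger things that the article does not support.

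- **That the 12-month NTB is discarded.** It is not. The extended model with its arm-by-time interaction can give a 24-month contrast that uses it.
- **That the primary effect is biased.** Nothing shows this. Drop-out rates that differ by arm do not by themselves cause bias, and equal dependence in both arms leaves almost none.
- **That the plan is in error for naming no missing-not-at-random analysis, or that every sensitivity analysis assumes missing at random.** Only the baseline-covariate adjustment clearly does. The mechanism and variables for multiple imputation are left open, and such detail commonly belongs in the statistical analysis plan, which the article promises and which is not shown.

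**Conclusion.** The point holds in a limited form. As published, the primary estimate relies on missing at random given arm, baseline NTB and site, and the only committed missing-data sensitivity analysis stays with baseline information. Drop-out driven by decline seen at 12 months is therefore not handled in the primary estimate, and no analysis that would handle it is designated for that purpose.

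The possible shift is about 0.02 at the planned 10% drop-out and about 0.04 at 20%, in either direction. It rests on an assumed log-odds of 1 per SD in one arm only and on assumed correlations with the 12-month score. It is negligible if the dependence is equal in both arms. The simulations place all drop-out after 12 months. For people lost before then the longitudinal model has no extra outcome to use, so its gain would be smaller. This is a worthwhile improvement in the choice of primary model, not a contradiction or a fatal flaw.

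**What to change.** Take the single primary 24-month contrast from the longitudinal model already planned: outcomes at 12 and 24 months, arm-by-visit and baseline-by-visit terms, site, unstructured within-person covariance, and the same facilitator clustering in the intervention arm. Keep the 24-month-only model as a sensitivity analysis. The endpoint does not change.

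If the primary model is to stay as it is, the minimum is to state that the 24-month contrast from the longitudinal model, or multiple imputation that includes 12-month NTB, will be reported as a committed missing-data sensitivity analysis. Either choice should be fixed before data analysis, so that the preference between models cannot follow the results.

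The cost is wording and modest analysis work, with no new data or visits. The downside is a slightly more complex covariance structure to fit alongside one-arm clustering. A delta-adjusted analysis, for example shifting imputed 24-month scores down by 0 to 0.6 in each arm separately and jointly and reporting the tipping point, would be a useful optional addition to the statistical analysis plan.
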